**Investigations on the elderly include:**

-Contents:

**Questionnaire: General Demographic Data:** Gender, age, ethnic group, education level, marital status, and medical insurance of the participant.

**Lifestyle Information:** Smoking, alcohol consumption, level of physical exercise, frequency of fruit and vegetable consumption.

**Level of Satisfaction in Meals:** How much they liked the meals provided by the nursing home, self-assessment of the level of saltiness in meals.

**Disease History:** Whether or not they are suffering from hypertension, diabetes, stroke, coronary heart disease, kidney disease, cancer, or COPD. As well as other disease histories and whether they are receiving treatment.

**Information on Antihypertensive Drugs:** Type, specification, and frequency of consumption of antihypertensive drugs.

**Occurrence of an Endpoint Event:** Whether or not there is all-cause mortality or cardiovascular events (coronary heart disease, congestive heart failure, heart arrhythmia, and stroke).

**Health Status:** Will be evaluated using the EuroQol Five Dimensions Questionnaire (EQ-5D).

**Physical Examination:** Weight, height, blood pressure, heart rate.

**Laboratory Examination:** Serum electrolytes (blood potassium), blood sugar and four items of blood lipid, kidney function (serum creatinine), and blood routine. Levels of 24-hr urinary sodium, urinary potassium, urinary creatinine, and quantitative microalbuminuria.

**Eye Fundus Examination:** Vision test and funduscopy.

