### **6.2 Secondary Outcome**

1. The incidence of hyperkalemia : as the main safety evaluation index. According to the 2012 Kidney Disease Improving Global Outcomes (Kidney Disease Improving Global Outcomes), serum potassium > 5.5 mmol/L is diagnosed as hyperkalemia; continuous measurement of serum potassium > 5.5 mmol/L is persistent hyperkalemia. Otherwise, it is a single attack.
2. The change in 24-hour urinary sodium、potassium and microalbumin
3. The change in diastolic blood pressure
4. European Five-Dimensional Health Scale (EQ-5D) score
5. Endpoint events (death, cardiovascular events (coronary heart disease, congestive heart failure, arrhythmia, stroke))
6. Fundus Atherosclerosis

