## **2.3 Outcome definitions**

The primary outcome for the study is SBP assessed as continuous variable (in mmHg) evaluated during 24-month follow-up.

Secondary outcomes:

- 1) DBP assessed as continuous variable (in mmHg) evaluated during 24-month follow-up.
- 2) 24-hour urinary sodium (in mmol/d), potassium (in mmol/d), and microalbumin excretion (In mg/d) assessed as continuous variable evaluated during 24-month follow-up.
- 3) Incidence of hyperkalemia. A new case of hyperkalemia is defined as having serum potassium  $>5.5$  mmol/L at either month 12 or 24 among participants with normal serum potassium at the baseline, regardless of clinical manifestations.
- 4) the risk of developing all-cause mortality, cardiovascular events (fatal and nonfatal stroke, fatal and nonfatal myocardial infarction, hospitalization or death caused by congestive heart failure)
- 5) ED-5Q during 24-month follow-up.

- 6) Incidence of renal dysfunction: A new case of renal dysfunction is defined as having eGFR <60 at either 12 or 24 months with normal eGFR at the baseline, regardless of clinical manifestations.
- 7) Incidence of hyponatremia: A new case of hyponatremia is defined as having serum sodium <135 mmol/L at either 12 or 24 months with normal serum sodium at the baseline, regardless of clinical manifestations.
- 8) A cost-effectiveness measure will be estimated based on the incremental cost of achieving each 1-mm Hg reduction in SBP

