### 5.2.2 Analysis for events

Frailty survival models (cox proportional hazards model with mixed effects) that account for within-cluster homogeneity will be used for the analysis of all-cause mortality, cardiovascular events (fatal and nonfatal stroke, fatal and nonfatal myocardial infarction, hospitalization or death caused by congestive heart failure). The proportional hazards assumption will be confirmed using statistics and graphs based on the Schoenfeld residuals. If more than one events took place during the study period, only the first event will be counted. Separated models will be built for each intervention, either SS alone or SSSC alone. The cluster(facility) will be regarded as the random effect. The models would be:

$$h_{ij}(t) = h_0(t)\exp(\beta_1 x_{ij} + \mu_j)$$

Where  $h_{ij}(t)$  is the hazard function for the  $i^{\text{th}}$  subject in  $j^{\text{th}}$  cluster.  $h_0(t)$  denotes the baseline hazard function. ;  $x_{ij}$ , the predictor of interest, either SS alone or SSSC alone, is an indicator of the intervention for subject  $i$  in cluster  $j$  (1 indicates receive intervention while 0 indicates not receive intervention);  $\beta_1$ , the coefficient of interest, is the effect coefficient of intervention;  $\mu_j$  denotes the random effect associated with the  $j^{\text{th}}$  cluster. An additional multivariate model will be conducted to controlling for the potential unbalanced covariates at baseline, if any.

The results for event will be presented in **Table 4** and **Table 5**.

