| 
The primary outcome for the study was the change in SBP from baseline to 2-year follow-up.
 
The primary analysis of intervention effects will use a generalized estimating equation with an exchangeable covariance structure accounting for clustering and adjustment for baseline SBP.
 | 
The primary outcome for the study is changed to SBP evaluated during 24-month follow-up.
 
A pre-specified linear mixed effects model will be performed to model repeated measures of SBP of the same individual over time.
 | 
To account for the impact of missing data due to high mortality and leaving from the residential facilities, all available follow-up data in SBP will be used instead of that just in 24-month alone. Thus, linear mixed model, which naturally fits to hierarchical data, is more appropriate than GEE in such situation.
 |
| 
Continuous secondary outcomes were changes in diastolic blood pressure; serum potassium; and 24-hour urinary sodium, potassium, and microalbumin excretion.
                                                                                                                                    | 
Like the primary outcome SBP, all continuous secondary outcomes are change to the mean level evaluated during 24-month follow-up
                                                                                                 | 
Same as above.
                                                                                                                                                                                                                                                                                                             |

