|                                                                                                                                                                                                                                                                                                       | 
Add secondary outcomes: Incidence of renal dysfunction: A new case of renal dysfunction is defined as having eGFR <60 at either 12 or 24 months, regardless of clinical manifestations.
                                       | 
We are particularly interested in the safety concerns about salt reduction strategies. Renal dysfunction is a potential side effect of salt reduction.
                                                                                                                                                                     |

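### The SAP narrows the protocol's cardiovascular outcome without recording the change, so the protocol-defined outcome goes unanalysed and nonfatal arrhythmia enters no planned randomized comparison

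*Supplement*

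**What the plan says.** Protocol V1.4, section 6.2 item 5, names as a secondary outcome "Endpoint events (death, cardiovascular events (coronary heart disease, congestive heart failure, arrhythmia, stroke". Section 5.2 records the same four disease types at the baseline assessment: "Whether or not there is all-cause mortality or cardiovascular events (coronary heart disease, congestive heart failure, heart arrhythmia, and stroke".

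SAP 2.3 item 4 replaces this with all-cause mortality and "cardiovascular events (fatal and nonfatal stroke, fatal and nonfatal myocardial infarction, hospitalization or death caused by congestive heart failure". SAP 5.2.2 carries that list into the frailty model, which analyses "all-cause mortality, cardiovascular events (fatal and nonfatal stroke, fatal and nonfatal myocardial infarction, hospitalization or death caused by congestive heart failure". Only a participant's first event counts, and the model is fitted separately for salt substitute (SS) and for stepwise salt supply control (SSSC).

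SAP 5.9 sets protocol text beside SAP text with a justification. It has three entries:
- "The primary outcome for the study is changed to SBP evaluated during 24-month follow-up", together with the change of model;
- "all continuous secondary outcomes are change to the mean level evaluated during 24-month follow-up";
- "Add secondary outcomes: Incidence of renal dysfunction".

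None of them concerns clinical events.

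**The concern.** A table of revisions with a justification column invites the reader to treat anything not listed as unchanged. Someone who trusts SAP 5.9 would take the cardiovascular hazard ratios in Tables 4 and 5 to be estimates for the protocol's outcome. They would be estimates for a narrower one, with no reason given for the narrowing.

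The practical stake is greatest for SS, the potassium-containing intervention. The protocol's event outcome would have set nonfatal arrhythmia in SS facilities against non-SS facilities as part of a composite. Under the SAP it would not appear in any between-group result, so the trial report could be silent on it whatever was recorded.

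**Working it through.** No figure in the plan bears on this. Neither document gives a cardiovascular event rate, count or hazard ratio, so the check is a comparison of texts.

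**Step 1: the components side by side.**

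| Protocol V1.4, 6.2 item 5 | SAP 2.3 item 4 and 5.2.2 | Change |
|---|---|---|
| Stroke | Stroke, fatal or nonfatal | Spelled out |
| Coronary heart disease | Myocardial infarction, fatal or nonfatal | Narrowed |
| Congestive heart failure | Hospitalization or death from it | Narrowed |
| Arrhythmia | None | Removed |
| Death | All-cause mortality | Kept |

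The protocol has four cardiovascular components and the SAP three. One is removed and two are narrowed, so 1 + 2 = 3 of the 4 differ.

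**Step 2: what follows for the composite.** Every SAP cardiovascular event also fits a protocol category: infarction is coronary disease, and a heart failure admission is heart failure. The protocol composite therefore has at least as many participants with an event as the SAP composite. Because only the first event counts, a participant's first protocol event falls no later than the first SAP event. Both counts and event times can differ. By how much, and what that does to the hazard ratio in either comparison, cannot be derived.

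**Step 3: is the change declared anywhere?** SAP 5.9 covers the primary outcome and its model, the continuous secondary outcomes, and the added renal outcome. The event sensitivity analysis in SAP 5.7 item 6 changes the population, not the definition. The table is incomplete in other respects too: hyponatremia is a new outcome in SAP 2.3 item 7, and the protocol's "Fundus Atherosclerosis" (6.2 item 6) is missing from SAP 2.3; 5.9 mentions neither.

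**Step 4: does arrhythmia come back elsewhere?**
- SAP 5.3.1 limits the safety outcomes to hyperkalemia, renal dysfunction, hyponatremia, and mean serum potassium and sodium.
- Tables 4 and 5 have rows for mortality and cardiovascular events only. Tables 6 and 7 have rows for the three incidence outcomes only.
- Protocol section 9 plans an SS against non-SS comparison of other adverse reactions. The SAP does not carry it over.
- The month 3 and month 6 monitoring in SAP 5.3.3 covers SS participants alone and concerns potassium and a questionnaire, so it offers no comparator.

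Nonfatal arrhythmia thus enters no planned randomized comparison. A fatal arrhythmia would still count under all-cause mortality.

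**Step 5: what potassium safety remains for SS?** Hyperkalemia incidence at month 12 or 24 (SAP 2.3 item 3, modelled in 5.3.2.1 with an adjusted secondary analysis), mean serum potassium (5.3.2.4) and all-cause mortality (5.2.2).

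**The case against.** **Operational definitions are ordinary SAP work.** The protocol gives bare disease labels, and turning them into countable events is what an SAP is for. A harder composite may well be the better endpoint. This stands as a reason to keep the narrower composite. It does not cover arrhythmia, which is removed rather than defined, and it does not excuse the silence in SAP 5.9.

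**SAP 5.9 may have been written against another description of the trial.** Its protocol column cites a generalized estimating equation, while V1.4 section 9 names a multilevel mixed-effects model. It also lists serum potassium among the continuous secondary outcomes, which V1.4 section 6.2 does not. This may explain the omission, and it means that the change cannot be dated to the writing of the SAP. The mismatch with the latest protocol remains.

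**Arrhythmia may not have been captured systematically.** The follow-up table in protocol 5.5 has no row for endpoint events. It shows hospitalization records at baseline and on transfer, and adverse reactions at any time; endpoint events are named explicitly only for early withdrawal. This stands, and limits how firmly the protocol composite can be read.

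**A reader might infer that the SAP strips out the event type most sensitive to potassium harm.** The documents do not say so. The protocol names hyperkalemia as its main safety index, and the SAP keeps it, with serum potassium and mortality.

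**A reader might also infer that the outcome was reshaped after results were seen in an unblinded trial.** SAP 5.7 and 5.9 do mention missing data in Xi'an and high mortality, so some follow-up experience was known. Neither is described by arm. SAP 2.4 says that the statistician holds the allocation codes, that only local intervention staff are informed, and that outcome assessors are independent of them. Knowledge of event results by arm is not shown.

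**Conclusion.** The point holds as a gap between protocol and SAP on a secondary outcome. Three of four cardiovascular components differ, SAP 5.9 does not record it, the protocol-defined outcome is not analysed, and nonfatal arrhythmia is in no planned randomized comparison.

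It does not touch the primary analysis: the trial is sized on systolic blood pressure (protocol section 10, SAP 2.5). It also does not show bias. With no event counts, there is no basis for saying that the cardiovascular hazard ratio would change direction, or that it favours either intervention. What is lost is completeness: the trial could report on SS safety without a between-group figure for an event type that its protocol named as an outcome.

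The conclusion takes V1.4 as the governing protocol and assumes that arrhythmias were recorded in some form. It should be addressed, and the added results matter more than the entry in 5.9, which alone would be documentation.

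**What to change.** 1. Keep the SAP composite as it stands.
2. Add the protocol-defined composite as a supportive row in Tables 4 and 5, with the same frailty model and first-event rule.
3. List recorded arrhythmia events by arm with the safety outcomes, stating how they were captured: hospitalization records, adverse-reaction reports or endpoint-event records.
4. Enter the change of definition in SAP 5.9, with its reason and its date relative to unblinding.

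The cost is SAP wording and a few table rows. The downside is that softer events may be less completely captured than infarction, stroke or admission for heart failure, so the added rows should be labelled supportive and read beside the statement on capture.

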## 7. Safety Considerations

### 7.1 Risk-Based Safety Monitoring and Management Plan

- **All participants will be screened for hyperkalemia and its related risk factors during the baseline investigation, Month 12 follow-up, and Month 24 follow-up.**

All participants enrolled in the trial will be tested for blood potassium and blood creatinine levels during the baseline investigation. Meanwhile, the information about the antihypertensive drugs (ACEI, ARB, potassium-sparing diuretics, etc.) taken by the participants will also be collected.

All participants enrolled in this trial will be tested once again for blood potassium and blood creatinine levels during the Month 12 and Month 24 follow-up.

- **Based on the results of the screening, any elderly who fit the clinical diagnostic criteria for hyperkalemia will be transferred to a local secondary hospital or above for further blood potassium and ECG testing. They will then be treated for hyperkalemia confirmed by the doctor. The elderly who are not diagnosed with hyperkalemia but fit any of the following conditions will be designated as the high risk group for monitoring.**

1. Participants with blood potassium  $>5.5\text{mmol/L}$ ;
2. Participants with  $15 \leq \text{eGFR} < 30\text{mL/min/1.73m}^2$  (Patients with Stage 4 chronic renal insufficiency).

The high risk group for monitoring will receive a blood potassium test every 3 months. Participants who are clinically diagnosed with hyperkalemia will be transferred to a local secondary hospital or above for hyperkalemia treatment. Participants who are not diagnosed with hyperkalemia will continue to be monitored for blood potassium 3 months later. The monitoring can be stopped temporarily should the blood potassium level of the participants  $\leq 5.5\text{mmol/L}$  in two consecutive tests. Otherwise, they will continue to be tested for blood potassium once every 3 months.

- **Blood potassium monitoring plan for the SS intervention group:**

All participants in the SS intervention group, aside from those who are confirmed to have

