## **2.2 Eligibility criteria**

Eligible participants were  $\geq 55$  years old at entry, expected to live in the facility for at least 2 years, and signed informed consent. Persons with physician-confirmed hyperkalemia, expected absence from the facility  $>1$  month per year, or incomplete blood pressure measurement at the baseline were excluded.

The number of ineligible participants, if any, will be reported, with reasons for ineligibility

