### 5.3.1 safety outcomes

The safety outcomes include:

- 1) Incidence of hyperkalemia;
- 2) Incidence of renal dysfunction;
- 3) Incidence of hyponatremia;
- 4) Mean serum potassium and sodium during follow-up

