### 5.3.2 Randomized comparisons

#### 5.3.2.1 Incidence of hyperkalemia

Only participants without hyperkalemia at baseline will be included in the study. A generalized linear mixed model accounting for clustering will be used for incidence of hyperkalemia

- 1) To evaluate the effect of SS or SSSC alone, the model will be:

The model will include intervention status as fixed effects, as well as cluster as random effects. Thus, the model would be:

$$\begin{aligned} \text{Logit}(P(y_{ij} = 1)) &= \beta_0 + \mu_j + \beta_1 x_{ij} + e_{ij} \\ e_{ij} &\sim N(0, \sigma_e^2) \\ \mu_j &\sim N(0, \sigma_{\mu_j}^2) \end{aligned}$$

Where  $i$  represents the  $i^{\text{th}}$  subjects,  $j$  represents the  $j^{\text{th}}$  cluster (facility),  $y_{ij}$  is the probability of hyperkalemia for subject  $i$  in cluster  $j$ ;  $\beta_0$  is the mean outcome in the control group;  $\mu_j$  is a cluster random effect to allow for between-cluster heterogeneity;  $x_{ij}$ , the predictor of interest, either SS or SSSC, is an indicator of the intervention for subject  $i$  in cluster  $j$  (1 indicates receive intervention while 0 indicates not receive intervention),  $\beta_1$ , the coefficient of interest, is the effect coefficient of intervention;  $e_{ij}$  is the random error for the measurement of subject  $i$  in cluster  $j$ .

2) To test the interaction effect of SS and SSSC, the model will be:

The model will include intervention status as fixed effects, as well as cluster as random effects. Thus, the model would be:

$$\begin{aligned} \text{Logit}(P(y_{ij} = 1)) &= \beta_0 + \mu_j + \beta_1 x_{1ij} + \beta_2 x_{2ij} + \beta_3 x_{1ij} * x_{2ij} + e_{ij} \\ e_{ij} &\sim N(0, \sigma_e^2) \\ \mu_j &\sim N(0, \sigma_{\mu_j}^2) \end{aligned}$$

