### 5.3.2.2 incidence of renal dysfunction

Analysis of incidence of renal dysfunction will follow the same approaches as that for incidence of hyperkalemia.

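### The SAP's only filtration outcome is a single unconfirmed eGFR below 60 from an undefined normal baseline, so loss of filtration in residents already below 60 has no named comparison

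*Supplement*

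**What the plan says.** **Definition.** SAP 2.3, item 6: "A new case of renal dysfunction is defined as having eGFR <60 at either 12 or 24 months with normal eGFR at the baseline". It gives no cut-point for normal, no minimum fall and no confirmatory value.

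**Second wording.** SAP 5.9 records the same outcome as an addition made in the SAP, namely eGFR below 60 "at either 12 or 24 months, regardless of clinical manifestations". No baseline condition appears there. Its stated reason is that renal dysfunction is a possible side effect of reducing salt.

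**Analysis.** SAP 5.3.2.2: "Analysis of incidence of renal dysfunction will follow the same approaches as that for incidence of hyperkalemia". The approach it copies, in SAP 5.3.2.1, removes baseline cases: "Only participants without hyperkalemia at baseline will be included in the study".

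**Who is enrolled.** SAP 2.2 starts its exclusions with "Persons with physician-confirmed hyperkalemia, expected absence from the facility" and names no renal criterion; nor does protocol 4.2. Protocol 7.1 (version 1.4) puts residents with eGFR from 15 to below 30, "Patients with Stage 4 chronic renal insufficiency", in a monitoring group. They are not excluded.

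**What is measured.** Protocol 7.1 tests everyone at baseline and again for "blood potassium and blood creatinine levels during the Month 12 and Month 24 follow-up".

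**Continuous safety outcomes.** SAP 5.3.1 lists "Mean serum potassium and sodium during follow-up". Neither eGFR nor creatinine is listed.

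**The concern.** The protocol's background says that the potassium-containing substitute might affect kidney function, and the SAP added a renal outcome for safety's sake. Residents with the least renal reserve are those in whom a further loss matters most. They are in the trial and their creatinine is measured, yet the one filtration outcome is built so that they cannot contribute to it.

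Among the others, the outcome keeps only which side of 60 a value falls on. A resident going from 61 to 59 is a case. One going from 95 to 62 is not, and neither is one going from 55 to 25. The crossing therefore discards much of what the creatinine values say about a shift in filtration.

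The two wordings add a practical problem. An analyst following SAP 2.3 drops residents below 60, while one following SAP 5.9 literally counts them as new cases. The two would report different numerators and denominators.

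**Working it through.** The documents give no rate, event count or power for the renal outcome, so there is no figure to reproduce. The structural part follows from the text. Sizing needs assumptions.

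**1. Does anything else cover residents below 60?**

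| Planned item | Where | Compares their filtration? |
|---|---|---|
| Incident eGFR below 60 | SAP 2.3, 5.3.2.2, Tables 6-7 | No; they are outside the at-risk set |
| Serum potassium and sodium | SAP 5.3.1, 5.3.2.4, Tables 2-3 | No; not a filtration measure |
| 24-hour microalbumin | SAP 2.3 item 2, Tables 2-3 | They contribute, but it is not a filtration measure |
| Subgroups by baseline eGFR stage | Protocol section 9; absent from SAP 5.6 | No; it stratifies other outcomes |

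Nothing fills the gap.

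**2. What can normal mean?** The only eGFR cut-point in the SAP is 60. It is the case threshold in 2.3 and marks an unhealthy condition in 5.3.2.1. A baseline of 60 or above is the natural reading, but it is not written down.

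**3. How many residents, and how much noise?** Assumed, not from the documents: true eGFR mean/SD of 80/18, 75/18 or 85/15; within-person CV of 6, 8 or 10%; no true change; normal read as 60 or above.

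- Measured baseline below 60, hence outside the outcome: about 5-22% of residents.
- Counted as incident by chance alone: about 2-11% of those at risk.

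A second set of assumptions used mean 75-90 with SD 15, or mean 80 with SD 20; CV 5-10%; and a true decline of 0-2 mL/min/1.73 m² per year. It put 3-19% outside, or about 25 to 180 of 960. Of the counted cases, 36-86% had a true eGFR that never fell below 60.

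**4. What would a continuous analysis add?** Take residents per side as 960/2 × (1 − 0.20) = 384, ignore clustering, and assume a uniform eGFR loss of 3 or 5 mL/min/1.73 m² on one side. One case by hand, with mean 80, SD 18 and CV 8%:

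- Error SD per value: 0.08 × 80 = 6.4. Error variance of the mean of months 12 and 24: 6.4²/2 = 20.5.
- Baseline reliability: 18²/(18² + 6.4²) = 324/365 = 0.888. True variance left after baseline adjustment: 324 × (1 − 0.888) = 36.4 (unrounded reliability).
- Residual SD: √(36.4 + 20.5) = 7.54. Standard error: 7.54 × √(2/384) = 0.544.
- Expected z: 3/0.544 = 5.5 and 5/0.544 = 9.2.

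Simulating the nine scenarios of step 3 with both losses gives 18 runs:

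| Analysis | Expected z over the 18 runs |
|---|---|
| Continuous eGFR, baseline-adjusted, all residents | about 4.2 to 12.5 |
| SAP crossing, at-risk residents only | about 1.6 to 3.9 |
| Fall of 30% or more from own baseline, all residents | about 0.2 to 2.9 |

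Clustering would lower all three. The table ranks the analyses; it is not a power statement.

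**The case against.** Several objections are sound.

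- **Removing prevalent cases is what incidence means.** The SAP does the same for hyperkalemia and hyponatremia. This stands: the exclusion is no error. The gap is that no companion outcome covers those it leaves out. Potassium and sodium each have one, because their means are also analysed.
- **It is not the only renal outcome.** Microalbumin is a secondary outcome with its own aim in SAP 1.2. This stands, so the point is limited to filtration.
- **A reader might infer that many counted cases will be measurement noise.** The documents do not show it. They give neither the eGFR distribution nor its variability, and a simulation with no true change makes every case false by construction. Noise of equal size in all groups favours none; it mainly pulls the relative risk toward 1.
- **A reader might prefer a 30% fall as the binary outcome.** It gives fewer false cases (0-1.1% under the first set of assumptions in the working), but its expected z was below that of the crossing in all 18 runs. The threshold has no source in the documents, and the rule would miss a fall from 61 to 43 (18/61 = 29.5%). It might do better for rare large falls, which these runs did not test.
- **Reading normal as 90 or above is strained.** Agreed, and one line settles it.
- **No conclusion of renal safety is planned.** True: SAP 2.6 tests for difference.

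**Conclusion.** The point holds for filtration. SAP 2.3 and 5.3.2.2 rest it on one unconfirmed threshold value from an undefined normal baseline. Residents already below 60 are eligible and have creatinine measured, but no named analysis compares their loss of filtration between groups. This follows from the text alone. How many residents are affected (about 5-22%), and how much sharper a continuous analysis would be, depend on the assumed eGFR mean, SD and CV and on a uniform loss.

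It would go too far to say that residents below 60 can never be cases: that is true of SAP 2.3 and 5.3.2.2, but SAP 5.9 read literally would count them. SAP 5.9 may be shorthand. Still, it describes the outcome that the SAP adopts, not superseded text, so the two must agree.

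This is a worthwhile repair to one safety outcome and leaves the primary SBP analysis untouched.

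**What to change.** 1. In SAP 2.3, 5.3.1 and 5.3.2.4, add eGFR during follow-up (months 12 and 24) as a continuous safety outcome in all residents with a baseline value. Use the mixed model already planned for serum potassium, with baseline eGFR as the covariate, and add a row beside serum potassium in Tables 2 and 3.
2. Keep the incidence of eGFR below 60. State its baseline condition as eGFR of 60 or above.
3. Align SAP 5.9 with SAP 2.3, so that both carry the same baseline condition.
4. Do not replace the crossing with a 30% fall.

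The cost is some SAP wording, one further model and one row in each of the two tables. It needs no new data and no change to conduct or participant monitoring.
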